# Examination of Web-Based Single-Session Growth Mindset Interventions for Reducing Adolescent Anxiety: Study Protocol of a 3-Arm Cluster Randomized Controlled Trial

**DOI:** 10.2196/41758

**Published:** 2023-03-17

**Keywords:** growth mindset, fixed mindset, mental health, secondary school students, brief intervention, belief-in-change

## Abstract

**Background:**

Anxiety disorders are the most common mental disorders worldwide. In Hong Kong, 7% of adolescents are diagnosed with anxiety disorders, and 1 in every 4 secondary school students reports clinical-level anxiety symptoms. However, 65% of them do not access services. Long waitlists in public services, the high cost of private services, or the fear of being stigmatized can hinder service access. The high prevalence of anxiety and low intervention uptake indicate a pressing need to develop timely, scalable, and potent interventions suitable for adolescents. Single-session interventions (SSIs) have the potential to be scalable interventions for diagnosable or subclinical psychopathology in adolescents. Providing precise and context-adapted intervention is the key to achieving intervention efficacy.

**Objective:**

This study aims to compare the effectiveness of three SSIs: single-session intervention of growth mindset on negative emotions (SIGMA), SSI of growth mindset of personality (SSI-GP), and active control, in reducing adolescent anxiety.

**Methods:**

Adolescents (N=549, ages 12-16 years) from secondary schools will be randomized to 1 of 3 intervention conditions: the SIGMA, SSI-GP, or active control. The implementation of each intervention is approximately 45 minutes in length. Adolescent participants will report anxiety symptoms (primary outcome), perceived control, hopelessness, attitude toward help-seeking, and psychological well-being at preintervention, the 2-week follow-up, and the 8-week follow-up. A pilot test has confirmed the feasibility and acceptability of SIGMA among adolescents. We hypothesized that SIGMA and SSI-GP will result in a larger reduction in anxiety symptoms than the control intervention during the posttest and 8-week follow-up period. We also predict that SIGMA will have a more significant effect than SSI-GP. We will use the intention-to-treat principle and linear regression-based maximum likelihood multilevel models for data analysis.

**Results:**

This study will be conducted from December 2022 to December 2023, with results expected to be available in January 2024.

**Conclusions:**

This protocol introduces the implementation content and strategies of growth mindset SSIs (consists of 2 forms: SIGMA and SSI-GP) among school students. The study will provide evidence on the efficacy of different growth mindset SSIs for adolescent anxiety. It will also establish implementation strategies for self-administrative SSIs among school students, which can serve as a pioneer implementation of a scalable and self-accessible brief intervention to improve the well-being of young people.

**Trial Registration:**

ClinicalTrials.gov NCT05027880; https://clinicaltrials.gov/ct2/show/NCT05027880

**International Registered Report Identifier (IRRID):**

PRR1-10.2196/41758

## Introduction

### Background

Anxiety is one of the leading causes of illness and disability among adolescents aged 10-19 years [1]. In the past decade, Hong Kong recorded a 6.9% prevalence rate of anxiety disorders with severe impairment [2], and 25% of youths were experiencing high subclinical anxiety symptoms in a 3-month period and required a clinical intervention [3]. Based on the prevalence and local youth population data [4], it can be roughly estimated that in Hong Kong there are 85,000 secondary students requiring help and intervention for their anxiety symptoms.

However, an estimated 65% of individuals with general anxiety disorders in Hong Kong do not access mental health services [5]. The median waiting time between the onset of symptoms and receiving public child and adolescent psychiatric service is 58 weeks, and the cost of seeking private treatment is reported HK$3000 (US $385) per monthly consultation, which means that many families have no choice but to wait for public services [6]. Lengthy waitlists or costly clinic-based treatments provided by highly trained mental health professionals may be difficult to disseminate on a broad scale. This traditional setting makes access to service more difficult in special circumstances, such as during the COVID-19 pandemic [7]. Moreover, adolescents with mental health symptoms are particularly vulnerable to stigma and discrimination and may not actively seek school-based interventions [8]. Even among youth who do access care, most drop out prematurely, completing just over 3 therapy sessions on average [9]. There is clearly a need to develop briefer, scalable, nonstigmatizing, and youth-friendly interventions for adolescents with general anxiety symptoms.

Single-session interventions (SSIs) are promising to be scalable, accessible, and cost-effective for youth’s mental health needs. SSIs refer to structured programs that intentionally involve only 1 visit or encounter with a clinic, provider, or program [10]. SSIs may serve as stand-alone or adjunctive clinical services. Emerging evidence supports the efficacy of SSIs in reducing and preventing youth’s mental health symptoms. For example, Schleider and Weisz [11] found that growth mindset SSIs led to more significant improvement in youth depression and perceived behavioral control in a 9-month follow-up than in active control. They also found that enhancing belief-in-change of personality-enhanced treatment access for adolescent depression [12], but recorded nonsignificant changes in general anxiety, social anxiety, and conduct problems [13].

A brief intervention can be effective if the intervention precisely addresses the underlying psychological process that contributes to the social or psychological problems [14]. Walton [14] and Wilson [15] underscore the importance of precise intervention and adaptive context to secure the potency of brief interventions. Brief interventions targeted to remove specific psychological barriers and produce recursive dynamics will affect long-term outcomes. Thus, the effectiveness of SSI is highly related to the implementation content (what to intervene) and strategies (how to implement). However, the existing SSIs vary in the effect size of effectiveness. Examining psychological mechanisms that address mental health more precisely and designing and implementing the intervention carefully will improve the efficacy of growth mindset SSIs.

This proposal aims to develop and examine the efficacy and effectiveness of growth mindset SSIs for adolescent anxiety in the Chinese context. It will advance the extant literature by implementing and comparing different domains of growth mindset and developing implementation strategies for SSI among Chinese adolescents. The existing growth mindset SSIs teach adolescents the growth mindset of personality (SSI-GP), which means the person can change. However, the effectiveness of SSIs for reducing anxiety was not as significant as reducing depression. Recently, Zhu et al [16,17] found the fixed mindset of negative emotions closely associated with adolescent depression and anxiety. Therefore, an intervention promoting growth mindsets of negative emotions may be a more precise factor in alleviating the worry and anxiety of adolescents, but it is not examined yet. Thus, this protocol presents our newly developed intervention: the single-session intervention for growth mindset on negative emotions (SIGMA) and compares its effectiveness with the SSI-GP and an active control.

The SIGMA, which aims to instill the belief that negative emotions can change, may address the need for a scalable intervention for reducing anxiety. It has 3 unique features. First, it is a mechanism-targeted intervention with a carefully constructed and theoretically precise program that directly addresses the belief of suffering symptoms. Therefore, it may also advance the existing growth mindset SSI in reducing worry about symptoms and increasing perceived control and hope. Second, SIGMA can be developmentally adapted and culturally adapted for adolescents. It will be particularly suitable for secondary school students with general anxiety due to the engaging nature of web-based interventions, videos, peer sharing, and nonstigmatizing feature. Third, the brevity and flexible format could make it attractive to those who might not otherwise access care, and for whom a targeted, “light touch” intervention might be just enough. Given the large need-to-access gap among youths, we propose this 3-arm randomized controlled trial to provide evidence on the effectiveness of SIMGA and compare it against the existing growth mindset intervention (SSI-GP) and support theory as an active control. See Figure 1 for the research design.

**Figure 1 figure1:**
[figure not shown]
Design of the 3-arm randomized controlled trial. SIGMA: single-session intervention of growth mindset for anxiety; SSI-GP: single-session intervention of growth mindset of personality; ST: support therapy.

### Aims and Objectives

The overarching goal of this study is to build the most effective implementation strategy of web-based growth mindset SSIs for reducing adolescent anxiety.

The primary objective of the proposed study is to evaluate the effectiveness of a SIGMA on reducing general anxiety symptoms in secondary school students. By using a 3-arm randomized control trial, we will compare the effectiveness of SIGMA to the SSI using growth mindset of personality (SSI-GP) and an active control condition using support therapy (ST).

The secondary objective is to compare the effectiveness of the aforementioned programs on secondary outcomes, including reducing hopelessness and increasing perceived control over emotions, attitude toward help-seeking, and psychological well-being.

There are 3 study hypotheses: (1) SIGMA and SSI-GP are more effective than the active control using ST in the primary outcomes, reducing general anxiety symptoms, and secondary outcomes, reducing hopelessness, enhancing perceived control, increasing positive attitude to help-seeking, and enhancing psychological well-being; (2) SIGMA is more effective than SSI-GP in the above primary and seconday outcomes; and (3) the effectiveness of SIGMA is greater in participants with higher motivation for change than in those with low to no motivation.

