### Sample Size Determination

To make sure the sample size is big enough to test the hypotheses, a small to medium effect size (Cohen *d*=0.33) is used based on prior research [11], power set at 0.80, and α set at .05. A final sample size of 438 (146 per arm) is required. With reference to the attrition rate of our previous studies in a school setting, which is less than 20%, there is a requirement to recruit 549 participants at the baseline (183 per arm).

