### Data Collection and Management

Assessments will be conducted by a blinded researcher trained in using the instruments. Self-rated scales will be completed by the participants under guidance. All the measures have been pilot-tested, and the questionnaires take about 20 minutes to be completed. Two attention-checking items will be included in the surveys of each time point for careless responding screening (eg, “Please choose *Strongly Agree* for this item”). Only those who answer both attention-checking items correctly each time will be included in the final data analysis [23]. As the literature has shown motivation playing pivotal roles in people’s behavioral change, we will also add 2 items at the beginning of the survey at baseline to assess participation motivation of our participants with a 6-point Likert scale, asking about their motivation to participate in this program and improve their emotion regulation ability, respectively.

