##### Motivation to Apply Things Learnt From the Program

Right after the intervention, we will ask participants after this program the extent to which they would like to apply the intervention content and the extent to which they would like to improve their emotion regulation on a 6-point Likert scale.

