### Data Analysis

An intention-to-treat analysis will be conducted for any missing data. Two-level analyses will be used to account for cluster randomization [37]. To examine the effects of the interventions, multilevel regression will be used to test the group effect, time effect, and their interaction effect on outcome measures. Additionally, we will calculate effect sizes using estimated marginal means; these effect sizes compare mean gain scores (Cohen *d*), reflecting changes in each outcome from baseline to 2 follow-ups for youths receiving the mindset versus active control interventions. The effect sizes will also be compared between participants in the intervention group who receive booster messages and those who do not. A *P* value of <.05 will be considered statistically significant, and SPSS version 26 (IBM Corp) will be used for all statistical analyses.

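### The sample-size statement covers all the hypotheses, but the calculation and the stated model do not reach hypothesis 3 (moderation by motivation)

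*Protocol article*

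**What the plan says.** All references are to the Protocol article.

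- **Aims and Objectives** numbers three hypotheses. The first two compare arms. The third is that "the effectiveness of SIGMA is greater in participants with higher motivation for change than in those with low to no motivation". Nothing there marks it as exploratory.
- **Sample Size Determination** begins "To make sure the sample size is big enough to test the hypotheses", takes a Cohen d of 0.33, with "power set at 0.80, and α set at .05", and concludes: "A final sample size of 438 (146 per arm) is required". Allowing for dropout, this becomes 183 per arm, 549 in all.
- **Data Collection and Management** adds two baseline items on a 6-point scale, "asking about their motivation to participate in this program and improve their emotion regulation ability, respectively".
- **Motivation to Apply Things Learnt From the Program**, which sits under Content Fidelity Checking, adds two items asked straight after the session. One concerns "the extent to which they would like to improve their emotion regulation on a 6-point Likert scale".
- **Data Analysis** says that "multilevel regression will be used to test the group effect, time effect, and their interaction effect on outcome measures". It also provides for comparing SIGMA participants with and without booster messages, and sets P<.05 as the threshold for significance. Motivation does not appear.
- **Limitations** mentions subgroup analyses, in the context of anxiety severity.

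**The concern.** A claim that an intervention works better in more motivated students is a claim about a difference between effects. It needs an interaction between arm and motivation, and its precision is not that of a main effect. The article says that the sample suffices for its hypotheses without exception, yet sizes only a comparison of two arms and describes a model in which motivation plays no part.

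Two things are at stake. A null result on hypothesis 3 could be read as evidence against moderation because the sample was said to be adequate, when it may say little. And with no interaction in the described model, the hypothesis either goes untested or is addressed by some analysis that the article does not describe. The main comparisons between arms are not affected.

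**Working it through.** **1. The plan's own figure.** Inputs from Sample Size Determination: d=0.33, power 0.80, alpha .05 (taken as two-sided).

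n per arm = 2 × ((1.960 + 0.842)/0.33)² = 144.2, so 145 by the normal approximation. The t-test solution is 145.1, which rounds up to 146. Power at 146 per arm is 0.802 (t-test) or 0.805 (normal). The one-sided version gives 114 and does not reproduce. For dropout, 146/0.80 = 182.5, so 183 per arm and 549 in all. The stated numbers are therefore right for two arms compared on a main effect, with no clustering allowance.

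**2. Hypothesis 3 with motivation split in two.** The documents give neither an interaction size nor a distribution of motivation, so both are assumed. Let p be the share with high motivation, with SIGMA against one other arm, 146 per arm, outcome SD 1, two-sided .05, no clustering and no baseline adjustment.

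SE = √[(2/146)(1/p + 1/(1−p))]; power = Φ(difference/SE − 1.96).

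With p=0.5, SE = √(8/146) = 0.234. For a difference of 0.33 SD, power = Φ(0.33/0.234 − 1.96) = Φ(−0.55) = 0.29. If the average effect is 0.33, that difference means about 0.50 in one half and 0.17 in the other (0.33 ± 0.165). The difference detectable with 80% power is 2.802 × 0.234 = 0.66 SD. For 0.33 SD at 80% power, n = 8 × (2.802/0.33)², about 577 per arm.

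**3. Hypothesis 3 with motivation kept continuous.** Per SD of motivation, SE = √(2/146) = 0.117. The slope detectable at 80% power is 2.802 × 0.117 = 0.33 SD per SD of motivation.

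To compare with step 2, assume a roughly normal score. The halves either side of the median then differ by 2 × 0.798 = 1.596 SD in mean motivation. A difference in effect of 0.33 between halves corresponds to a slope of 0.33/1.596 = 0.207. Power = Φ(0.207/0.117 − 1.96) = Φ(−0.19) = 0.42.

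**4. Sensitivity of the split analysis.**

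| Assumption | Power |
|---|---|
| 0.33 SD; split 50:50, 30:70, 20:80 | 29%, 25%, 20% |
| 0.165 SD; same splits | 11%, 9%, 8% |
| 0.66 SD; same splits | 80%, 73%, 62% |
| 0.33 SD, 50:50, both other arms pooled | 37% |
| 0.33 SD, 50:50, no dropout (183 per arm) | 35% |
| 0.33 SD, 50:50, one-sided test | 41% |
| 0.33 SD, 50:50, baseline–outcome correlation 0.5 to 0.7 | 37% to 51% |
| 0.33 SD, 50:50, class ICC 0.01 to 0.05, about 24 analysed per class | 25% to 16% |

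The last row applies the whole design effect to the interaction, which is conservative.

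**5. The model.** Group, time and group-by-time estimate how arms differ in change over time, averaged over motivation. No coefficient in that model says whether the SIGMA effect varies with motivation.

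**The case against.** The strongest reply is that this is a journal article. The moderator term, comparator, follow-up and any multiplicity rule commonly belong in an analysis plan, which is not shown. That stands for those details taken singly. It does not rescue the sample-size sentence, which makes a positive claim that its own calculation does not support. Nor is Data Analysis merely brief: it finds room for the booster comparison, which is not among the three hypotheses, and gives nothing for one that is.

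Several stronger readings are tempting and should be resisted.

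- *Power is 29% where 80% was stated.* A reader might infer this, but no power is stated for hypothesis 3 by itself, and 80% is correct for the main effect. The 29% depends on a dichotomy, an even split, a 0.33 SD difference and no baseline adjustment. The split calculations run from 8% to 80%.
- *The moderator is not named.* It is: motivation for change, with two baseline items introduced because motivation matters for behaviour change. What is open is which item or combination is meant.
- *Post-session items will define the subgroups.* They are placed under fidelity checking and nothing proposes them as moderators.
- *The hypothesis is confirmatory.* That word is not used. The stated objectives, the Abstract and the Discussion's expectations do not mention moderation by motivation; only the numbered list puts it beside the main comparisons.
- *The false-positive rate is several times .05.* Such a figure counts any success among many item, comparator and follow-up combinations. The article describes no such search, and a two-sided count includes results opposite to a directional hypothesis.

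**Conclusion.** The point holds in a limited form. The sample-size statement is broader than its calculation: 146 per arm supports a comparison of two arms at d=0.33 and does not establish adequacy for hypothesis 3. The described model, followed as written, does not test that hypothesis.

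The size of the shortfall can only be illustrated. For a 0.33 SD difference in effect between motivation halves, power is about 29% with an even split, or about 42% with a continuous, roughly normal score, both before clustering and baseline adjustment. At that difference every split-based variant checked stays below 80%. Reaching 80% takes a strong interaction: 0.66 SD between equal halves (for example 0.66 in one and zero in the other), or a change of 0.33 SD per SD of motivation. The Discussion itself expects a small effect. This deserves correction, but it does not threaten the primary comparison.

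**What to change.** 1. **Sample Size Determination:** limit the 80% statement to pairwise comparisons of arms at d=0.33. State separately that the detectable interaction for hypothesis 3 is about 0.33 SD per SD of motivation at 80% power, before any clustering allowance. The figure of 0.66 SD belongs only to a 50:50 split and should not be quoted for a continuous analysis.
2. **Aims and Objectives:** label hypothesis 3 exploratory.
3. **Data Analysis:** add one arm × time × motivation interaction with its lower-order terms. Use a baseline motivation measure from Data Collection and Management, chosen in advance and kept continuous, with one named comparator and one named follow-up. Report the interaction with its 95% CI and do not judge it by P values within subgroups. A sentence confirming that the post-session items are not used as moderators would cost nothing.

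The cost is a few sentences and one extended model, with no new data or participants. The downside is that hypothesis 3 ceases to be a headline claim and the power statement reads less favourably.

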## Methods

### Research Design

This study will use a cluster-randomized control trial design. A conceptual model is provided in Figure 1. The intervention protocol will be pre-registered before data collection in ClinicalTrials.gov (ref: NCT05027880), and strictly follow the CONSORT (Consolidated Standards of Reporting Trials) guidelines [18,19]. At least 3 classes in the same grade of the participating school will be randomized (using computer-generated random numbers) into the (1) SIGMA group, (2) SSI-GP group, and (3) ST group (active control condition group), which will provide ST intervention at the same time. All participants will receive regular interventions in school. Three repeated assessments of the measures will be conducted for the 3 groups simultaneously at (1) baseline, (2) 2-week postintervention, and (3) 8-week postintervention (Figure 2). The cluster randomization at the classroom level can balance the risk of contamination between the intervention and active control groups and the school heterogeneity due to the school culture, schedule, and management.

**Figure 2 figure2:**
[figure not shown]
CONSORT (Consolidated Standards of Reporting Trials) diagram reflecting the flow of participants through this study. SIGMA: single-session intervention of growth mindset for anxiety; SSI-GP: single-session intervention of growth mindset of personality; ST: support therapy.

### Sample Size Determination

To make sure the sample size is big enough to test the hypotheses, a small to medium effect size (Cohen *d*=0.33) is used based on prior research [11], power set at 0.80, and α set at .05. A final sample size of 438 (146 per arm) is required. With reference to the attrition rate of our previous studies in a school setting, which is less than 20%, there is a requirement to recruit 549 participants at the baseline (183 per arm).

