## Discussion

### Overview

We anticipate that SIGMA, which highlights that emotion states are changeable, will significantly enhance the growth mindset of emotion and reduce general anxiety symptoms and secondary outcomes compared to SSI-GP and the active control. However, the effect size will be small because single-session self-help interventions are low-dosage interventions. SSI-GP is hypothesized to have better outcomes than the active control group. The half with booster messages in the SIGMA group will have better outcomes than the half without boosters, especially in the 8-week follow-up.

To date, this will be one of the few randomized controlled trials to apply a single-session growth mindset intervention to reduce anxiety. As focusing on the key aspects and using effective ways to make changes are the key mechanism of effective SSI, addressing the key aspects that can secure changes is essential for designing SSIs. This 3-arm randomized controlled trial will help elucidate the mechanisms of change in adolescent anxiety symptoms: believing that negative emotion can change (SIGMA), believing that personality can change (SSI-GP), or receiving support (active control). This proposed study will find the potent core element of brief intervention in helping youth with anxiety.

This study will also be a pioneer study examining the self-administered web-based intervention among Chinese adolescents. There is a paucity of research in the Chinese context on effective implementation strategies for self-administrative SSI. As the effect size of SSI varies from small to medium in extant interventions, the dedicated design and careful implementation matter in the efficacy of the study. This study will provide a clear protocol of implementation content and strategies, which will be helpful for the future use and development of SSIs.

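### The 146-per-arm sample size is an individually randomised calculation with a design effect of 1, so it does not support the stated 80% power for a trial that randomises classes

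*Protocol article*

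**What the plan says.** The Sample Size Determination section opens with the aim "To make sure the sample size is big enough to test the hypotheses". It says "a small to medium effect size (Cohen *d*=0.33) is used based on prior research [11"], with "power set at 0.80, and α set at .05", and concludes "A final sample size of 438 (146 per arm) is required". Allowing for attrition below 20%, it sets recruitment at 549, or 183 per arm. No ICC, class size, number of classes or design effect appears.

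The Research Design section states "This study will use a cluster-randomized control trial design". Under Participant Eligibility and Randomized Control Process there are 6 schools with a minimum of three classes each. The three selected classes are randomised to the three conditions, and all students in a class share one condition. About 60% of students are expected to take part, giving roughly 90 per school. The Data Analysis section plans two-level analyses for the clustering, a group-by-time multilevel regression, and effect sizes on gain scores.

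The hypotheses under Aims and Objectives include each growth mindset intervention against the active control and SIGMA against SSI-GP. The Overview of the Discussion expects that "the effect size will be small because single-session self-help interventions are low-dosage interventions".

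**The concern.** Students in one class tend to resemble each other, and the class is the unit allocated. The variance of an arm difference then depends on the ICC, the class size and the number of classes. A sample size that treats students as independent omits a variance component that the planned analysis will include. The declared 80% would then be a property of a different design, and a reader weighing a null result would rely on a power figure the trial has not shown it has.

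A second, smaller issue is that a single d=0.33 is offered for all the hypotheses. The article does not say which contrast it belongs to, and gives no separate basis for the comparison of the two growth mindset arms.

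**Working it through.** **1. Reproduce the stated figure.** Inputs from Sample Size Determination: d=0.33, α=.05 (two-sided assumed), power 0.80. A two-sample t-test needs 145.11 per arm, so 146; power at 146 is 80.2%. Times three is 438. Attrition: 146/0.8 = 182.5, so 183; times three is 549. Both figures match exactly, so no design effect is contained in either. Other versions do not match: one-sided gives 114 to 115 per arm, Bonferroni 175 (two comparisons) or 193 (three), and the three-group ANOVA versions tried give totals of about 357, 401 or 534.

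**2. Number of classes.** 6 schools × 3 classes = 18, or 6 per arm, is a minimum. Other figures in the article point higher. About 90 participants at 60% consent means 90/0.6 = 150 invited per school, which is 50 per class if there are only three. The Implementation Strategies section describes groups of around 12 to 20. If each group were a class, 90/20 = 4.5 to 90/12 = 7.5 classes per school, or 27 to 45 in all. I therefore show 18 and 36 classes.

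**3. Apply clustering.** The ICC is not in the article; I assume 0.01 to 0.05. Design effect DE = 1 + (m − 1) × ICC, with m = 146/6 = 24.3 or 146/12 = 12.2 completers per class. The variance of the standardised difference is 2 × DE/146. Power uses d = 0.33 with either a normal or a noncentral t reference. The t degrees of freedom are classes − 3 arms − 5 school contrasts: 10 for 18 classes and 28 for 36.

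| ICC | DE, 18 classes | Power, normal | Power, 10 df | DE, 36 classes | Power, normal | Power, 28 df |
|---|---|---|---|---|---|---|
| 0.01 | 1.23 | 72% | 63% | 1.11 | 76% | 73% |
| 0.02 | 1.47 | 64% | 56% | 1.22 | 72% | 69% |
| 0.03 | 1.70 | 58% | 50% | 1.33 | 68% | 65% |
| 0.05 | 2.17 | 48% | 41% | 1.56 | 62% | 59% |

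These are unadjusted, single-time-point figures. If school effects are not fitted, df = 18 − 3 = 15 and the 18-class row becomes 66%, 59%, 53% and 43%.

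**4. Allow for baseline.** Assume a baseline correlation r=0.6, with the same reduction at student and class level. ANCOVA multiplies the variance by 1 − r² = 0.64; gain scores multiply it by 2(1 − r) = 0.8. School effects are fitted. Power at ICC 0.01/0.02/0.03/0.05:

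- ANCOVA, 18 classes: 82/75/68/58%
- ANCOVA, 36 classes: 90/87/84/78%
- Gain scores, 18 classes: 73/65/59/49%

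**5. SIGMA versus SSI-GP.** The article states no effect size for this contrast. Purely as an illustration, an assumed d=0.20 with 146 per arm gives 40% power before any clustering.

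**The case against.** The strongest reply is that the trial need not be underpowered. The class count is a floor, the planned model uses baseline, and attrition may be below 20%. Much of this stands. With 36 classes, ANCOVA and r=0.6, power exceeds 80% up to ICC 0.03. A reader might infer from the 18-class figures that 80% holds only for an ICC of about 0.01 or less. The article does not support that, because it does not fix 18 classes. The 10 df are also a choice: the Data Analysis section names no school effects, and fitting them would remove between-school variance from the relevant ICC. With normal critical values, ANCOVA at 18 classes and ICC 0.02 gives 83%.

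None of this rescues the stated calculation. Sample Size Determination mentions neither baseline nor the number of classes, and its figure comes out exactly with independent students. The gain-score comparison named in Data Analysis also recovers less than ANCOVA. Nor is this a detail lost in condensing a full protocol into an article: no fuller text could turn 146 into a cluster-based number.

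A reader might also infer that the small effect expected in the Discussion contradicts a small-to-medium d=0.33, or that the SIGMA versus SSI-GP contrast has 40% power. Neither follows. The two descriptions overlap, and d=0.20 is not in the article.

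Finally, the analysis does plan for clustering, so the point concerns power and not the validity of the test.

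**Conclusion.** The point holds as a fault in the power statement. The arithmetic is right for individual randomisation, but that is not this trial's design, so 80% is unsupported as written. That conclusion needs no outside figure. The size of the shortfall does: it depends on an assumed ICC of 0.01 to 0.05 and on a class count the article leaves open. Without baseline adjustment, power is below 80% in every case in the table, from 41% (18 classes, ICC 0.05, 10 df) to 76% (36 classes, ICC 0.01, normal). With baseline used at an assumed r=0.6 it runs from 49% to 90%, depending on method, ICC and class count. It would therefore be too strong to say that the trial cannot reach 80%; what can be said is that the article has not shown that it does.

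**What to change.** Replace the power statement with a cluster-based one. It should give the number of classes per arm, the expected completers per class, an ICC range with its source, how baseline enters the primary comparison (ANCOVA or change), and the degrees of freedom. Then restate the power, or the detectable d, that 438 completers provide, as a range over ICC and class count. Say which contrast d=0.33 applies to, and report power for SIGMA versus SSI-GP separately under an effect range labelled as assumed. If the same students can be spread over more classes, show the gain: at ICC 0.03, unadjusted with school effects fitted, 36 classes give 65% against 50% for 18.

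The cost is one rewritten paragraph and a less favourable stated power. No extra participants are needed.
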